### Data management

All data collected from individuals will include a specific personal identifier code for the individual. Laboratory data will be paper-captured before they are double entered into electronic databases by trained local data entry clerks at PHL-IdC. Double entered data will be cleaned by an epidemiologist at Swiss TPH. All discrepant electronic data will be returned to the local data entry clerks, who will trace back the personal identifier code in the original paper forms, re-enter the discrepant results and return the corrected data so that the final datasets can be generated. Registration, questionnaire and additional diagnostic data will be entered directly into the questionnaire software ODK using a tablet computer (Samsung Galaxy Tab A 2019) and subsequently uploaded on a secure server. The personal identifier code will be used to merge registration, questionnaire and laboratory examination data from each individual. Only coded data will be statistically analysed. To report the laboratory results back to the individuals, coded data can be linked with the participant names.

Data entered into electronic databases will only be accessible to authorized personnel directly involved with the study by use of a protected password. Hard copies of the source data such as student registries, laboratory record sheets, ICFs and assent forms will remain at the PHL-IdC in Pemba, respectively, for at least 10 years and stored at a safe place. The electronic versions of the data entries as well as electronic-captured data will be uploaded to and stored on a secure server from Swiss TPH.

### Statistical methods

To analyse the primary outcome, we define the sensitivity of the surveillance system as the proportion of cases detected:$${\text{SE}} = {\text{N}}_{{{\text{inf detected by surveillance}}}} / {\text{N}}_{{{\text{inf}}}}$$

The total number of infected persons is unknown but will be estimated from the cross-sectional surveys as:$${\text{N}}_{{{\text{inf}}}} = {\text{ P}}_{{{\text{school}}}} *{\text{ N}}_{{{\text{school}}}} + {\text{ P}}_{{{\text{non}} - {\text{school}}}} *{\text{ N}}_{{ {\text{non}} - {\text{school}}}}$$whereby prevalences (P) and corresponding confidence intervals are estimated via generalized estimating equations for binary data with independent correlation structure to account for correlation within clusters.

The prevalence and intensity of *S. haematobium* infections will be calculated by different diagnostic approaches used in the annual cross-sectional surveys. Intensity of infection will be classified into light (< 50 eggs/10 ml urine) and heavy (≥ 50 eggs/10 ml urine) according to thresholds provided by the WHO for urine filtration results [3].

The timeliness of case notification and reactive intervention will be assessed by recording the time needed from diagnosis to treatment, from diagnosis to follow-up of *S. haematobium* positive individuals and test-and-treat of their household members, and from diagnosis to reactive snail control.

The acceptability of the surveillance-response approach will be assessed by a mixed methods approach based on the results of questionnaires run in parallel to test-and-treat approaches in low-prevalence shehias.

The coverage of test-and-treat activities will be calculated by assessing the number of people who were targeted by test-and-treat activities in relation to the total population.

MDA coverage will be calculated by assessing the number of people reporting in the cross-sectional surveys that they received praziquantel during the last MDA in relation to the total number of participants in the cross-sectional surveys.

MDA compliance in hotspot areas will be calculated by assessing the number of people reporting in the cross-sectional surveys that they have taken praziquantel as recommended, in relation to the total number of participants in the cross-sectional surveys.

The impact of snail control will be determined by assessing the snail abundance and number of intermediate host snails at each HWCS identified over time during regular snail surveys.

The impact of behaviour change interventions in schools will be evaluated by assessing knowledge, attitude and practices of schoolchildren over time based on questionnaires.

The impact of the intervention approaches on the *S. haematobium* prevalence will be analysed descriptively.

The diagnostic accuracy of new PoC tests will be calculated by determining the proportion of individuals that have been correctly identified as *S. haematobium*-infected (sensitivity) and the proportion of individuals that have been correctly identified as negative (specificity) in comparison with the reference test.

The number and location of schools, madrassas, health facilities, and water bodies and the abundance of intermediate host snails of the genus *Bulinus* identified by micro-mapping of the IUs, will be analysed descriptively.

Statistical analyses will be carried out with the statistical software STATA and R.

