### Primary and secondary objectives

The primary objective of this study is to quantify the sensitivity of an adaptive surveillance-response approach for its ability to detect *S. haematobium* infected individuals in low-prevalence areas to trigger an appropriate intervention response. The primary outcome variable will be the number of *S. haematobium* infected individuals detected and reported through the surveillance approach divided by the number of positive individuals in the population as extrapolated from the cross-sectional surveys, i.e. the mean sensitivity of the surveillance-response approach determined over 3 years.

Secondary outcome analyses will cover additional performance parameters of the surveillance approach, as defined by WHO [45]. Moreover, we will assess the impact of multi-disciplinary interventions in hotspot areas, as well as the coverage of test-and-treat activities in low-prevalence areas and of MDA in hotspot areas. Other secondary outcomes will include the accuracy of several diagnostic approaches and micro-mapping of characteristics of the study shehias, including the number and location of schools, madrassas (Islamic schools), and health facilities, the number and location of water bodies and the abundance of intermediate host snails of the genus *Bulinus*.

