**Fig. 2 Fig2:**
[figure not shown]
Twenty study shehias (implementation unit) of the SchistoBreak project in Wete and Micheweni districts in Pemba, Tanzania. The image base map (United Republic of Tanzania – Subnational administrative boundaries) was downloaded from OCHA services (https://data.humdata.org/dataset/tanzania-administrative-boundaries-level-1-to-3-regions-districts-and-wards-with-2012-population). The data source is: Tanzania National Bureau of Statistics/UN OCHA ROSA. The data are published under the following license: Creative Commons Attribution for Intergovernmental Organisations (CC BY-IGO; (https://creativecommons.org/licenses/by/3.0/igo/legalcode)). Additionally, we received written permission to use and adapt the data from the UN Office for the Coordination of Humanitarian Affairs (OCHA). Additional shape files for the map (shehia boundaries) were provided by the Zanzibar Commission of Lands to the Zanzibar Neglected Diseases Programme

The study will take place in communities, schools and health facilities. In Zanzibar, public primary schools contain the grades 1–6 and some schools include a nursery school. In addition, most of the children in Zanzibar visit a madrassa [48]. The net enrolment rate in primary schools was 68.4% in Micheweni and 81.9% in Wete in 2014/15 [49].

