### Annual cross-sectional parasitological surveys

The annual cross-sectional surveys will be implemented in all 20 communities and their main public primary schools at sub-district shehia level. This micro-mapping approach will allow us to determine *S. haematobium* prevalences in the school-aged population, which is at highest risk of schistosomiasis, as well as in the whole community to get an accurate picture of infection levels in preschool-aged children, school-aged children, adolescents and adults. The cross-sectional surveys will serve to stratify the study area into low-prevalence and hotspot IUs and hence to micro-target the interventions according to pre-set prevalence thresholds. Moreover, the cross-sectional surveys will allow to determine and monitor the performance of the surveillance-response approach and impact of interventions over the study period. Participants of the annual cross-sectional parasitological surveys identified as infected with *S. haematobium* will be offered treatment with praziquantel (40 mg/kg using a dose pole) [50].

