### Annual community-based parasitological surveys

#### Selection of houses and participants

For the annual community-based surveys, 70 housing structures per shehia will be selected by a computer-based randomisation procedure from Geographical Information System (GIS) shape files provided by the Zanzibar Mapping Initiative (http://www.zanzibarmapping.com) of the Commission of Lands Zanzibar. Randomly selected housing structures will be located by field enumerators by using the navigation app Maps.me (https://www.maps.me/) combined with ODK installed on a computer tablet (Samsung Galaxy Tab A 2019). Accounting for a 30% dropout of housing structures that may not be inhabited (i.e. shops, sheds, mosques, houses under construction or abandoned houses) and households without any member willing to participate, we estimate that we will have a final sample size of 50 houses per shehia included in the survey. People sharing the same kitchen or pot will define a household. All household members meeting the inclusion criteria will be invited to participate in the survey and to provide one own urine sample, which will be examined for *S. haematobium* infection markers. With an average of five people per household, we estimate to collect urine samples from a total of 250 participants per shehia. Additionally, one adult household member present at the first visit to the house will be invited to participate in a questionnaire survey to assess household characteristics. If more than one adult is present and eligible to participate at first visit, we will randomly select the participant of the questionnaire survey by using a playing-cards approach.

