#### Data collection

A field enumerator using ODK and the wayfinding app Maps.me will visit each selected housing structure. The geolocation of each housing structure will be recorded in ODK. If the house is inhabited, the study will be explained in lay terms to the present household members and they will be invited to participate in the survey. Information and consent forms (ICF) for all eligible household members and assent forms for children aged 12 to 18 years will be distributed. Once adult participants and in the case of children aged below 18 years their parents provided written informed consent by signing the form and, additionally, once children aged 12 to 18 years agreed to participate by signing the child assent form, plastic containers (100 ml) for urine collection will be distributed for each participant. The plastic containers will be labelled with a unique identifier code and an individual sticker picture, which both match the same identifier code and sticker picture on a provided paper form containing the household member names to support their correct identification. Additionally, one adult household member will be invited to answer several questions related to participation in the last MDA, water contact behaviour, access to safe water sources, opinion regarding intervention approaches against schistosomiasis, and the number of individuals living in the household and their main demographic information, such as sex and age. On the following day, the study team will revisit the households and collect the (remaining) signed ICFs, signed assent forms and filled urine containers. Each shehia will be visited for three days, to cover all selected houses and ensure maximal participation and compliance with urine collection.

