### School-based parasitological surveys

#### Selection of participants

The annual school-based cross sectional survey will be conducted in the main public primary school of each shehia. If a shehia has several public primary schools, the school with most students will be surveyed. If a shehia has no public primary school, no school will be surveyed. In each of the schools, a total of 175 students aged 4–17 years will be randomly selected for urine collection. For this purpose, one class of each nursery and standard 1–6 grades, will be selected based on computer-randomised lists. In the selected classes, all children will line up, stratified by sex. Subsequently, we will systematically select each third child in the lines to be included in the study until 25 children per class are reached. This procedure will be continued until we reach a total of 175 selected children from the 7 selected grades. Accounting for a 20% drop-out due to non-consenting parents, absenteeism of children or inability to produce a urine sample of sufficient volume, we aim for a final sample size of 20 children per standard (i.e. a total of 140 students per school).

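### The primary-outcome denominator N_inf keeps infected people whom the survey itself offers to treat before surveillance starts, and it states no shehia index or size weights

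*Protocol article*

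**What the plan says.** Under Primary and secondary objectives, the primary outcome is the number of infected people detected through surveillance, "divided by the number of positive individuals in the population as extrapolated from the cross-sectional surveys", averaged over three years. Statistical methods gives the denominator as N_inf = P_school × N_school + P_non-school × N_non-school, where "prevalences (P) and corresponding confidence intervals are estimated via generalized estimating equations for binary data with independent correlation structure". That section names no shehia index, no weights, no cluster unit and no source sample for the non-school term.

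Two surveys feed the formula. In the school survey, "In each of the schools, a total of 175 students aged 4–17 years will be randomly selected for urine collection", with 140 expected to contribute. In the community survey, "All household members meeting the inclusion criteria will be invited to participate in the survey", with 50 houses and about 250 people expected per shehia. Neither target varies with shehia size.

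The section on annual cross-sectional parasitological surveys says that participants found infected "will be offered treatment with praziquantel". The same section, and Interventions and data collection, use the survey results to decide which shehias are low-prevalence units and so receive surveillance-response.

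**The concern.** A survey positive is counted in N_inf but is not among the cases detected by surveillance. Once treated and cured, that person stays in the denominator and can no longer enter the numerator. Measured sensitivity is then too low for a reason unrelated to how well surveillance works.

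The second issue is scale. Fixed samples mean that an unweighted pooled P gives each shehia about the same weight, while the total N counts each shehia by its size. The product equals the sum of shehia-level case counts only if prevalence and size are unrelated. The formula has no index, and the outcome is a single mean sensitivity, so pooling is a natural reading, although the article does not state it.

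The study's headline result rests on this ratio. The Discussion adopts it because the study is not powered to show changes in prevalence.

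**Working it through.** **Inputs.** 140 pupils and 250 community members per shehia, 20 shehias and 4,000 inhabitants per shehia (Sample size); about 3,900 per shehia (Study setting). Individual shehia sizes and the inputs of the sample-size simulation are not given.

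**The plan's own figure.** 20 × (140 + 250) = 7,800. As a share of the population, 7,800 / (20 × 4,000) = 9.75%, or 7,800 / (20 × 3,900) = 10.0%. The stated total and its share of about 10% both reproduce.

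**Survey-treated cases.**
- If survey participants are as likely to be infected as other residents, the survey finds a fraction f = 390/4,000 = 0.0975 of the positives in N_inf.
- If all are treated and cured before surveillance and none is reinfected, the ceiling on measured sensitivity is 1 − f = 0.90.
- A sensitivity of 0.50 among the cases that remain reads 0.50 × 0.9025 = 0.45.
- The school sample over-represents pupils. Assume 3% prevalence in pupils, 1% in others and 1,000 pupils among 4,000 residents. Then N_inf = 30 + 30 = 60. The community survey finds 250 × 60/4,000 = 3.75. The school survey adds 140 × 0.03 × (1 − 250/4,000) = 3.94 after allowing for people in both. The share is 7.69/60 = 12.8%. With 600 to 1,400 pupils it runs from 13.8% down to 12.0%, so the ceiling is about 0.86 to 0.88.
- The overlap falls where surveillance looks. The survey and active case finding both use the largest public primary school. The survey expects 3 × 20 = 60 pupils in grades 3–5, against an estimated 450 covered by active surveillance: 60/450 = 13%.

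**Size weighting, if P is pooled.** Take two shehias of 2,600 and 5,200 (assumed; mean 3,900) with equal samples.

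| Prevalence, small / large | Sum of N_i × P_i | Pooled P × total N | Bias in N_inf |
|---|---|---|---|
| 1.5% / 0.5% | 39 + 26 = 65 | 1.0% × 7,800 = 78 | +20% |
| 0.5% / 1.5% | 13 + 78 = 91 | 78 | −14% |
| 1.0% / 1.0% | 26 + 52 = 78 | 78 | 0 |

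In general the relative bias is 1/(1 + ρ × CV_N × CV_P) − 1, where ρ is the correlation between size and prevalence. Assumed values of ρ = ±0.2, CV_N = 0.3 and CV_P = 0.7 give a product of ±0.042 and a bias of about 4% either way. With ρ = ±0.4, CV_N = 0.5 and CV_P = 1.0 it runs from −17% to +25%.

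**The plan's bias check.** The Sample size section reports a median bias of zero. It compares sensitivity under the apparent prevalence from the surveys with sensitivity under the apparent prevalence from surveillance. That definition mentions neither treatment of survey positives nor weighting, so it does not settle either point.

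**The case against.** Survey positives do belong to the infected population at the time of the survey, and the outcome definition counts positives in the population. Depletion also needs the offer to be accepted, the infection to be cured and no reinfection to follow. The timeline figure is not available, so the interval between survey and surveillance is unknown. All of this limits the size of the effect. It does not remove it: the order of events follows from the survey's role in classifying shehias, and no section takes the treated cases out.

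On weighting, the formula could be applied per shehia. Shehia populations are collected in the shehia characteristics survey, and weights may be set out in an analysis plan. This stands, and the point is therefore conditional on pooling. Independence working correlation with a robust variance is a valid choice and is not criticised.

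Two stronger readings are tempting.

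- **That no survey measures non-school prevalence, so whole-community prevalence fills that term and pupils' risk counts twice.** The article does not say this. The community survey includes non-pupils and aims at an "accurate picture of infection levels in preschool-aged children, school-aged children, adolescents and adults", so a non-pupil subset can be analysed. What is missing is the definition. The household items listed are "the number of individuals living in the household and their main demographic information, such as sex and age", which are examples and may not be the full form. Since "The net enrolment rate in primary schools was 68.4% in Micheweni and 81.9% in Wete in 2014/15", age alone would be an imperfect proxy for attendance.
- **That shehia is treated as the cluster, which makes the standard errors too wide.** Statistical methods never names the cluster, so that inflation cannot be attributed to the plan.

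**Conclusion.** The point holds in two parts of different strength. Retention of survey-treated cases follows from the text. It lowers measured sensitivity by up to about 10% in relative terms, or 12–14% if pupils have three times the prevalence of others (3% against 1%, assumed). These are upper-end figures that assume full treatment and cure before surveillance and no reinfection.

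The weighting part applies only if P is pooled without weights. Its size cannot be fixed from the article because shehia sizes are not given: −14% to +20% in the assumed 2:1 example, and zero if size and prevalence are unrelated. The two effects are separate and may add or partly offset.

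The non-school group needs a definition, but the article does not show that it is being estimated wrongly. The corrections are cheap and bear on the primary outcome, so they should be made.

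**What to change.** Amend the N_inf paragraph in Statistical methods as follows.

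1. Define the school and non-school groups so that they do not overlap, and say which pupils N_school counts and how a shehia without a surveyed school enters. Estimate each prevalence from all survey participants in its group, keeping the positives in. Take P_non-school only from community participants who are not pupils, and record school attendance if the form does not already do so.
2. Compute N_inf per shehia and sum, or weight participants by N_i/n_i within each group, using the population and school sizes already collected.
3. From the total N_inf, subtract the count of survey positives actually treated, from both the school and the community survey, counting once anyone found in both. Do this after estimating the prevalences: dropping treated positives from the estimation sample would push P towards zero. State how a treated person whom surveillance later finds positive is handled, so that numerator and denominator stay aligned.
4. Report sensitivity with the unsubtracted N_inf as a sensitivity analysis. The two results bracket the effect of incomplete cure.
5. Name the cluster unit used for the confidence interval.

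The cost is analysis wording, a slightly wider interval from weighting and, if needed, one extra question on the tablet form. Nothing changes in how participants are treated.

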### Participant eligibility

All individuals who meet the following inclusion criteria are eligible to participate in the study:All persons aged ≥ 4 years, living in the study shehias.Submitted informed consent form (ICF) signed by parent or legal guardian in case of participating children and adolescents, or signed by the participant in case of participating adults, and submitted assent form in case of children aged 12 years and older signed by the participating children.Urine sample with sufficient volume to perform diagnostic tests provided.

All individuals who do not meet the following exclusion criteria are not eligible to participate in the study:Children < 4 years.Children, adolescents and adults not living in the study area.ICF not submitted or not signed by parent or legal guardian in case of participating children or adolescents or not signed by the participant in case of participating adults. Assent form not submitted or not signed by the child in case of participating children aged 12 years or older.No urine sample of sufficient volume to perform diagnostic tests provided.

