Third, to control the morbidity due to schistosomiasis, WHO provides several thresholds based on the baseline prevalence among school-aged children to decide upon the treatment strategy and frequency of MDA [3, 4]. However, to our knowledge, with regard to the schistosomiasis elimination goals, official thresholds indicating when to increase the frequency of MDA, or stop large-scale MDA and change tactics to surveillance strategies for detecting elimination or resurgence of transmission are not yet published, but urgently needed. These intervention thresholds for elimination settings should ideally be available for or transferable to a set of different diagnostic methods, which, depending on their sensitivity and specificity, will reveal different prevalences in the same population. Cross-diagnostic threshold adaptation has been evaluated for several standard tests used for the identification of both *S. haematobium* and *S. mansoni*, but only for thresholds at 10% prevalence, with samples from school-aged children, and in settings with higher intensity of infections than in Zanzibar [62, 63]. In our study, the thresholds to stratify low-prevalence IUs and hotspot IUs and the implementation of respective intervention approaches are predicated on single urine filtration results in our cross-sectional surveys and an analytical picture of the micro-epidemiology of urogenital schistosomiasis in Zanzibar established over the past 10 years. Due to age-dependent exposure rates [6, 64], we have initially selected thresholds determining hotspot IUs at ≥ 3% prevalence in individuals aged ≥ 4 years sampled in community-based surveys and at ≥ 2% *S. haematobium* prevalence in schoolchildren sampled in school-based surveys. The suggested thresholds will be subject to change and adaptation over the course of the project, i.e. in case we observe a considerable increase of prevalence in the low-prevalence IUs targeted with surveillance response.

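### The non-school prevalence behind the primary denominator describes those who gave urine; weighting to the household age and sex listing would be a cheap improvement

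*Protocol article*

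**What the plan says.** All references are to the Protocol article.

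- **Target.** Primary and secondary objectives defines the outcome as cases found by surveillance "divided by the number of positive individuals in the population as extrapolated from the cross-sectional surveys".
- **Formula.** Statistical methods states: "The total number of infected persons is unknown but will be estimated from the cross-sectional surveys as" N_inf = P_school × N_school + P_non-school × N_non-school.
- **Estimator.** In the same section, "prevalences (P) and corresponding confidence intervals are estimated via generalized estimating equations for binary data with independent correlation structure". The stated reason is clustering. No covariate, sampling weight or response weight is named, and none is ruled out.
- **Who is sampled.** Selection of houses and participants: "70 housing structures per shehia will be selected by a computer-based randomisation procedure", and "All household members meeting the inclusion criteria will be invited to participate in the survey".
- **Who is counted.** Participant eligibility requires signed consent, and also: "Urine sample with sufficient volume to perform diagnostic tests provided". In the community survey, remaining forms and urine containers are collected at a revisit the next day (Data collection).
- **What is known about everyone in the house.** One adult per household is asked for "the number of individuals living in the household and their main demographic information, such as sex and age".
- **Age and infection.** The Discussion explains the separate school and community thresholds with the words "Due to age-dependent exposure rates".

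**The concern.** The count is extrapolated to residents, but the prevalence comes from participants. A GEE with an independence working correlation widens or narrows the interval for clustering; it does not change who is represented. If, within the non-school stratum, the groups that take part more readily are also more or less often infected, P_non-school is shifted, N_inf shifts with it, and the sensitivity moves inversely. A participation pattern that recurs under the same collection procedure would not be averaged out over the three years.

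The school/non-school split does not settle this. Study setting reports net primary enrolment of 68.4% in Micheweni and 81.9% in Wete, so about 32% and 18% of primary-age children were not enrolled. They fall in the non-school stratum together with preschool children, older adolescents and adults. The split also does nothing for differences by sex. The age and sex needed to correct unequal participation within households are collected, but the article does not say they are used here.

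**Working it through.** **1. The plan's own figures.** 20 × (140 + 250) = 7800, as stated. 70 × 0.7 = 49, given as 50 houses; 50 × 5 = 250 community participants per shehia; 175 × 0.8 = 140 pupils. The 30% allowance is for whole structures and for households with no willing member. The step from 50 houses to 250 people makes no allowance for members of a participating house who give no urine.

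**2. What the stated GEE returns.** With an intercept only and independence, the estimating equation is Σ(y − p) = 0, so p is the pooled proportion. A simulated dataset of 15 clusters of 250 gave 0.0136 from the GEE and 0.0136 from the pooled proportion.

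**3. Bias within the non-school stratum.** For two groups with population shares c and 1 − c, prevalences p1 and p2, and participation r1 and r2:

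expected P = (c·r1·p1 + (1 − c)·r2·p2) / (c·r1 + (1 − c)·r2); true P = c·p1 + (1 − c)·p2.

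The article gives none of these inputs; all are assumed.

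- *Age:* 20% youths at 2.5%, adults at 1%, participation 85% and 55%. Youth share among participants = 0.17 / (0.17 + 0.44) = 0.279. Expected P = 0.279 × 2.5% + 0.721 × 1% = 1.418%. True P = 1.30%. Ratio 1.09.
- *Sex:* equal numbers, men 1.5% and women 0.7%, participation 45% and 75%. Expected P = (0.45 × 1.5% + 0.75 × 0.7%) / 1.20 = 1.00%. True P = 1.10%. Ratio 0.91.
- *Range:* low-participation group 30–50% of the stratum, its relative participation 0.5–0.9, its prevalence ratio 0.33–3. The ratio of expected to true P runs from 0.83 to 1.17. With relative participation 0.9 it stays within 0.97 to 1.03. With equal prevalence it is exactly 1.

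**4. Effect on N_inf and sensitivity.** Population 15 × 4,000 = 60,000 (Sample size). Assumed: 30% school at 2%, 70% non-school at 1%, true sensitivity 0.40.

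N_inf = 18,000 × 0.02 + 42,000 × 0.01 = 360 + 420 = 780.

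| Non-school P, relative to truth | N_inf | Sensitivity |
|---|---|---|
| 1.09 | 360 + 458 = 818 (+5%) | 0.40 × 780/818 = 0.38 |
| 0.91 | 360 + 382 = 742 (−5%) | 0.40 × 780/742 = 0.42 |
| 1.17 | 360 + 491 = 851 | 0.37 |
| 0.83 | 360 + 349 = 709 | 0.44 |
| 1.03 | 360 + 433 = 793 | 0.39 |
| 0.97 | 360 + 407 = 767 | 0.41 |

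Using the age example's own 1.30% for the non-school stratum changes little: 360 + 546 = 906 becomes 360 + 595.6 = 955.6, which is +5.5% and a sensitivity of 0.38.

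**The case against.** - **The formula already stratifies.** The contrast the article stresses, pupils against everyone else, is separated and scaled to its own population total. This stands. It limits the point to the non-school stratum and dilutes its effect on N_inf.
- **No input is documented.** Participation and prevalence by age and sex are not given, so neither the size nor the direction of any bias is shown. This also stands.
- **Fieldwork aims at high participation.** All eligible members are invited, and each shehia is visited for three days to maximise compliance. This makes near-equal participation plausible, in which case the bias is about 3% or less. It does not establish it.
- **The article is condensed.** Weights or covariates may be set out in a full protocol or analysis plan that is not shown. This has force. But the article does fix the estimator, down to its working correlation, with clustering as its only purpose. The point is therefore an improvement to a stated estimator rather than a charge of omission.
- **The listing is limited.** It comes from one adult per house and cannot correct refusal by whole households. The article names sex and age, not pupil status. Participation rates by age and sex can still be computed from all listed eligible members and applied to non-school participants, if participation within a cell does not depend on pupil status.
- **Positives are few.** At an assumed 1%, 15 × 250 × 0.70 = 2,625 non-school participants yield about 26 positives a year. Fine weighting cells would be unstable; broad ones are needed.
- **The simulations showed a median bias of zero.** The factors that Sample size lists as varied are prevalence, clustering, test accuracy and surveillance performance. Participation is not among them, so that result does not bear on this point.

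**Conclusion.** The point holds as a modest, inexpensive improvement to the primary analysis. As stated, P_non-school represents consenting urine providers and is scaled to all non-school residents. Under the assumed age example it is about 9% too high and N_inf about 5% too high, so a sensitivity of 0.40 reads as about 0.38. The assumed sex example gives about the same error in the opposite direction.

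A reader might infer more than the documents support, in two ways:

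- *That one average over all ages is multiplied up, so that any imbalance passes in full into N_inf.* Pooling 45% of residents aged 4–17 at 2.5% with adults at 1%, at the same participation rates, would give 1.84/1.675 = 1.10, and harsher assumptions would give more. The stated formula separates school from non-school, so such mixes do not describe it, and an error in one stratum reaches N_inf only in part.
- *That a bias, or a constant direction over the years, has been demonstrated.* With unchanged procedures a recurring pattern is plausible, but the article contains no data on it.

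**What to change.** State in Statistical methods that the community participants used for P_non-school will be weighted by the inverse of their participation rate within age-group-by-sex cells, or post-stratified to those cells, using listed household members of eligible age (4 years and over). Use broad cells. Enter the weighted P_non-school in N_inf. Report participation by age and sex each year, and give the unweighted estimate as a sensitivity analysis.

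The cost is one weighting step on data already collected and a slightly larger variance. Non-participation of whole households remains uncorrected and should be reported separately.
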